#### Analysis of the key secondary outcome (periodontitis sub-study)

The key secondary outcome of the percentage of periodontal sites with PPD ≥ 5 mm at 6 months, for participants included in the periodontitis sub-study, will be analysed using a linear mixed-effects model adjusted for the primary outcome and for baseline percentage of sites with PPD ≥ 5 mm.

Missing data mechanisms will be considered, and sensitivity analyses may be carried out on an imputed dataset— these will be pre-specified in the SAP.

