### Objectives

The primary objective is to compare biochemically verified smoking abstinence at 6 months of NRT and EC interventions to usual care (VBA) and to each other in adult regular tobacco smokers attending an NHS dental setting.

The key secondary objective is to compare the periodontal health at 6 months of NRT and EC interventions to usual care and to each other, for those with periodontitis at baseline. Other secondary objectives include assessing: smoking abstinence at 12 months, oral health, cost-effectiveness, patient quality of life, and intervention acceptability and associated experiences of the patients and dental professionals. We will also compare the occurrence of pre-specified AEs.

An 8-month internal pilot tested the feasibility of site recruitment and set-up, participant recruitment, and monitored the proportion of participants recruited to the periodontitis sub-study.

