### Trial outcomes

#### Primary outcome

Biochemically verified smoking abstinence at 6 months from baseline visit (an established measure of long-term smoking abstinence) using a carbon monoxide monitor. An expired air carbon monoxide (eCO) reading of 10 parts per million (ppm) or above signifies smoking tobacco.

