***Periodontitis sub-study – Biological Sample collection***							
Sub gingival dental plaque		***X***^***P***^				**X**^Q^	
Buccal brush biopsy		***X***^***P***^				**X**^Q^	
Unstimulated saliva (exploratory data collection in selected sites only)		***X***^***P***^				**X**^Q^	
Calculus sample (exploratory data collection in selected sites only)		***X***^***P***^				**X**^Q^	

**= if randomised to NRT or EC $=If randomised to NRT group only*

^@^* =The follow-up visits are scheduled around the usual 6 monthly recall visits that would be recommended for someone with a risk factor such as tobacco smoking. Ideally this should fall 6 and 12 months from the baseline visit, but no specific visit timing parameters are defined*

^P^*=Baseline: before (maximum of 28 days prior) or on the day of delivery of the intervention*

^Q^*= on the same day as, or a maximum of 28 days after, the 6-month follow-up visit conducted by the primary care team*

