### Periodontal sub-study

Additional assessments will be conducted at baseline and 6-month visits for the participants in the periodontal sub-study. These will be conducted by the regional hub assessors, who are blinded to the participant’s trial randomisation group and smoking status. Training sessions were held for the examiners (dentist, dental therapist or dental hygienist) and dental nurses from each hub before the first patient recruitment, in the form of an in-person training event in the Newcastle Dental Clinical Research Facility. A range of examiner alignment activities were undertaken. Inter-examiner agreement was assessed against a gold standard, at the mouth level, to ensure the reliability of the inputs to the statistical models for the final analyses. Repeat measures were used to assess intra-examiner reliability. Live data were presented during the sessions, and additional training and repeat exercises completed where necessary. If new examiners join the study, they will be required to complete the examiner alignment activities individually.

The assessments that will be conducted by the hub assessors at baseline and 6 months on participants in the periodontal sub-study are listed in the schedule of events (Table 2).

Sub-study participants will receive an additional £20 voucher on completion of baseline and 6-month assessments. Assessors from the hub will visit the participant’s dental practice to perform the assessments, or in some cases the participant may travel to the hub, in which case they will receive a further additional incentive in the form of a £20 gift voucher to cover any travel expenses.

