#### Analysis of all other secondary outcomes

The binary secondary outcome measures, such as continuous biochemically verified smoking abstinence at 12 months, will be analysed using a mixed-effects logistic regression model. Numerical secondary outcome measures, such as Oral Health Quality of Life Assessment score, will be analysed using a linear mixed-effects regression model. All models will be adjusted as for the primary outcome, with the addition of the adjustment for the baseline of that outcome if available. Details will be given in the pre-specified Statistical Analysis Plan (SAP).

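### As printed, the key secondary model adjusts the 6-month periodontal outcome for 6-month abstinence, a post-randomisation variable; the wording is probably a slip and needs correcting

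*Protocol article*

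**What the plan says.** The section on the key secondary outcome says that the percentage of sites with PPD ≥ 5 mm at 6 months will be "analysed using a linear mixed-effects model adjusted for the primary outcome and for baseline percentage of sites" with PPD ≥ 5 mm. It names no other covariate and no random effect.

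The Primary outcome section defines that outcome as "Biochemically verified smoking abstinence at 6 months from baseline visit". In Table 2, the sub-study examination takes place "on the same day as, or a maximum of 28 days after, the 6-month follow-up visit conducted by the primary care team". The named covariate therefore belongs to essentially the same time point as the outcome being modelled.

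The Objectives section sets the aim for those with periodontitis: to "compare the periodontal health at 6 months of NRT and EC interventions to usual care and to each other". General analysis principles sets intention to treat.

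Two neighbouring sections describe adjustment differently. The primary analysis adjusts for the two stratification factors, with hub/region random and baseline periodontal status fixed. The section on all other secondary outcomes says: "All models will be adjusted as for the primary outcome, with the addition of the adjustment for the baseline of that outcome if available".

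**The concern.** Abstinence at 6 months is a consequence of allocation. The Background section itself says that smoking raises the risk of periodontitis and impairs its treatment, so quitting is a route by which NRT or an e-cigarette could change gum health. Conditioning on it has two effects.

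- The part of the arm difference that runs through quitting is taken out of the arm coefficient.
- Quitters are compared with quitters, and non-quitters with non-quitters. These groups are not randomised. Anything that influences both quitting and periodontal health, such as motivation or oral hygiene, then biases what is left.

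The covariate is also partly set by rule, because missing abstinence data count as smoking.

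This is the trial's only key secondary outcome. It appears in the abstract, and p < 0.05 will be called significant. A result from the literal model could be read as evidence on periodontal benefit or harm when it answers a different question.

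**Working it through.** **1. What the document fixes.** It gives no target difference, SD or sample size for the periodontal outcome, so there is no stated figure to reproduce on this point. The abstinence rates used below come from the Sample size section: 6% for VBA and a difference of 7 points, hence 13%. That calculation does reproduce. With allocation 1:2, the pooled rate is (0.06 + 2 × 0.13)/3 = 0.1067, and

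n(VBA) = [1.960 × √(0.1067 × 0.8933 × 1.5) + 1.036 × √(0.06 × 0.94 + 0.13 × 0.87/2)]² / 0.07² = 242.2, rounded up to 243.

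Then 243 + 486 + 486 = 1215, as stated.

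**2. Total and direct effect.** Let q be the effect of quitting on the percentage of deep sites and d any effect of allocation not through quitting. Both are assumptions. With no shared cause of quitting and gum health:

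- total effect of allocation = (0.13 − 0.06) × q + d
- arm coefficient with abstinence in the model = d

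The table sets these beside simulations of 2,000,000 participants each, fitted by least squares on arm and baseline value, with and without abstinence. The hub effect was left out; it does not bear on the point. The simulation error is about 0.016 points: √(10² + 3²)/√(2,000,000 × 2/9), using a residual SD of 10 and the shared cause in step 3.

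| q | d | True total | Model without abstinence | Model with abstinence |
|---|---|---|---|---|
| −10 | 0 | −0.70 | −0.70 | 0.00 |
| −5 | 0 | −0.35 | −0.36 | 0.00 |
| −10 | −1 | −1.70 | −1.67 | −0.97 |
| −10 | +1 | +0.30 | +0.34 | +1.04 |

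In the last row the estimate moves away from zero.

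**3. Adding a shared cause.** Suppose an unmeasured trait U (standard normal) has correlation 0.5 with the liability to quit and lowers the outcome by 3 points per SD, with q = −10 and d = 0. The normal density at the 6% and 13% cut-offs is 0.1191 and 0.2115. The mean of U is then:

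- non-quitters: VBA −0.5 × 0.1191/0.94 = −0.063; active −0.5 × 0.2115/0.87 = −0.122
- quitters: VBA 0.5 × 0.1191/0.06 = 0.993; active 0.5 × 0.2115/0.13 = 0.814

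Within either group the active arm has the lower mean of U, so it looks worse by 3 × 0.058 = 0.17 points (non-quitters) and 3 × 0.179 = 0.54 points (quitters). Least squares weights the groups in the ratio 0.203 to 0.016, giving (0.17 × 0.203 + 0.54 × 0.016)/0.219 ≈ +0.20. The simulation gave +0.23, against −0.67 without abstinence (true −0.70). A second set-up (log-odds of quitting 1 per SD, −4 points per SD) gave +0.26 against −0.69 for q = −10, and +0.27 against −0.34 for q = −5.

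**4. Which reading was meant?** Set side by side, the sentence for the key secondary outcome and the one for the other secondary outcomes have the same two parts in the same order: the primary outcome, then the baseline value. The first lacks only the word *as*. It also specifies a mixed-effects model without naming a random effect, and the only random effect named in the statistical analysis section is hub/region, in the primary model. With *as* restored, the sentence has a random effect and agrees with its neighbours and with intention to treat. No passage states a mediation or direct-effect aim for this outcome.

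**The case against.** The strongest objection is that this is a typographical slip and nobody intends to adjust for abstinence. Step 4 supports that, and the unseen full protocol or SAP may already have the right wording. A reader might infer that the investigators have chosen to condition on a mediator; the document does not support that. What remains is that the sentence is grammatical and can be carried out as it stands. The section with the better wording covers only the other secondary outcomes, so it does not formally correct this one.

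Three stronger readings also fall.

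- **That the adjustment removes the treatment effect.** This holds only if allocation acts wholly through quitting. The article treats possible effects of e-cigarettes on oral health as a question in its own right.
- **That the bias is towards no effect.** The row with d = +1 shows the opposite, and reversal of sign needs an assumed shared cause.
- **That the strata were left out as a separate defect.** Their absence follows from the same wording. Restoring the word brings both back, including hub, which matters here because the sub-study assessments are done by hub: "These will be conducted by the regional hub assessors".

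A further objection is that the practical loss may be modest. A shared cause worth 4 points per SD, if not captured by the baseline value, implies a residual SD of at least 4. Even with all 243 v 486 participants the standard error would be 4 × √(1/243 + 1/486) = 0.31, so two-sided 5% power would be at most about 61% for 0.70 points and 20% for 0.35. The sub-study is smaller than that, and the article already calls its non-primary comparisons unpowered. This stands. A correct model would also often miss differences of this size, but that does not justify estimating the wrong quantity.

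**Conclusion.** The concern holds for the sentence as printed. Carried out literally, the key secondary model conditions on a post-randomisation variable on the pathway and does not estimate the total effect of allocation that the objectives and intention to treat require. It gives a direct-effect estimate open to confounding, with bias possible in either direction.

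The size cannot be fixed from the document. In the illustration (6% v 13% abstinence, quit effect −10 points, no direct effect), −0.70 becomes about 0.00, or about +0.2 to +0.3 with an assumed shared cause. The quit effect, the direct effect and the shared cause are all assumptions.

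Confidence is high about what the words say. It is much lower that they express the intended analysis; a dropped word is the more likely explanation.

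**What to change.** Reword the sentence so that the key secondary model is adjusted as for the primary outcome (research hub/region as a random effect, baseline periodontal status as a fixed effect) and for the baseline percentage of sites with PPD ≥ 5 mm. State explicitly that 6-month abstinence is not a covariate, and confirm that the full protocol and SAP say the same.

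If the investigators do want a model that includes abstinence, it should be a separate analysis, labelled as exploratory mediation, with its assumptions about shared causes stated.

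The cost is one sentence in the article and a check of the SAP, best done before any unblinded analysis. It needs no new data.

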#### Analysis of all other secondary outcomes

The binary secondary outcome measures, such as continuous biochemically verified smoking abstinence at 12 months, will be analysed using a mixed-effects logistic regression model. Numerical secondary outcome measures, such as Oral Health Quality of Life Assessment score, will be analysed using a linear mixed-effects regression model. All models will be adjusted as for the primary outcome, with the addition of the adjustment for the baseline of that outcome if available. Details will be given in the pre-specified Statistical Analysis Plan (SAP).

#### Interim analyses

There are no formal interim analyses planned in this trial.

#### Additional analyses

An analysis investigating socioeconomic inequalities in participation in the ENHANCE-D trial will be carried out as part of a related sub-study.

### Economic evaluation

The health economic component will include an economic evaluation in the form of a cost-effectiveness analysis (CEA) and a cost–benefit analysis (CBA). The economic evaluation will be conducted according to best practice guidelines [43].

The CEA will use the trial primary outcome (smoking abstinence) as the outcome measure. Alongside the CEA, a CBA will also be conducted using a measure of willingness-to-pay (WTP) for the interventions and primary outcome (smoking abstinence at 6 months). WTP values for the CBA will be elicited via a contingent valuation study (CVS), in which preferences for each intervention and the primary outcome are obtained. The CBA will be administered at 6 months via an online survey, either completed at the practice visit or at home by participants. The survey will take the form of a payment card [44]. The values used in the CVS were informed by the relevant literature, trial team and PPI representatives.

Data will be collected within the trial and used to calculate costs and estimate outcomes for the CEA. The interventions will be micro-costed, and bespoke participant questionnaires (Healthcare Utilisation Questionnaire) and eCRF will capture data on medications (only medications related to smoking cessation and managing any symptoms associated with smoking cessation will be considered), dental service use, and other subsequent healthcare service use. Participant questionnaires, created using input from the PPI representatives, will be administered at baseline and 6 months post-randomisation to capture service use. Unit costs for these services will be obtained from routine data sources and trial-specific estimates [45]. The analysis will be conducted from an NHS and personal and social services perspective. Unit costs will be combined with service use to estimate costs per participant in each randomisation group of the trial. Sensitivity analyses will estimate the costs incurred by participants in the trial. Participant costs will be collected as part of the participant questionnaires.

For the CEA, the results will be presented as point estimates of mean incremental costs and effects. Regression analysis will be applied to costs and effects to estimate adjusted point estimates of incremental costs, effects and cost-effectiveness [46]. Stochastic analyses (plots of cost and effects and cost-effectiveness acceptability curves) using bootstrapping techniques will be conducted to explore uncertainty in the estimate of cost-effectiveness [47–49]. The results of the CBA will be presented as incremental costs and effects (effectiveness will be estimated by the mean WTP for smoking cessation multiplied by the primary outcome) and incremental net benefits, where net benefits = incremental effects – incremental costs. The results of the CBA will also be used to estimate the net benefits of each intervention which will be determined by mean WTP of the intervention – mean costs of the intervention.

Deterministic sensitivity analyses will be performed to explore key uncertainties. Where appropriate, these analyses will be combined with a stochastic analysis with the results presented as described above. Missing data is expected from the trial; methods of imputation to address missing data will be determined once the full dataset is available [50]. Both the CEA and CBA will include an assessment of the distribution of outcomes according to socioeconomic status to explore any possible impacts of the intervention on inequalities.

An analysis of the periodontitis sub-study will use the same methods as described above for the CEA. This analysis will be largely exploratory as it is expected that the sub-study sample size will be insufficient for robust conclusions to be drawn on cost-effectiveness.

### Qualitative evaluation

A qualitative study within the main trial will explore participants’ experiences of receiving the study interventions whilst incorporating the views of dental professionals and NHS commissioners or service managers. The latter groups may identify additional facilitators or barriers to these interventions being adopted in NHS primary dental care. The study will adopt Normalisation Process Theory [51] (NPT) to guide data interpretation. NPT comprises four constructs: Coherence, Cognitive Participation, Collective Action, and Reflexive Monitoring [52]. This qualitative study may involve up to 32 patients, 16 dental professionals, and 5 NHS commissioners. These indicative numbers are based upon predictions linked to purposive maximum variation sampling, including the variables of sex, age, UK region, the dental practice where the intervention is delivered, and patients representing all trial randomisation groups. Based upon the authors’ collective experiences of conducting qualitative research in dental settings, it is anticipated that theoretical saturation is likely to be achieved by the numbers stated above. The sample will include a range of dental team members involved with delivering the trial interventions and working under different NHS dental contractual regulations. Selected participants recruited via purposive maximum variation sampling will be invited to participate in this qualitative study at two time points: at approximately 1 month following initial receipt of their allocated intervention and after their 6-month appointment. Dental professionals will be invited to participate on the same basis, but NHS commissioners/service managers will be interviewed once at approximately 9–12 months following the start of trial recruitment.

Qualitative data collection methods will offer a choice of face-to-face or online semi-structured interviews, telephone interviews, or focus group meetings. All interviews and focus groups will be audio-recorded, following the structure outlined in topic guides customised to each participant group based upon the research team’s prior experience in this area of study (see Additional File 3). Topic guides will be revised during the data collection process if required. Interviews and focus groups will be led and analysed initially by a single experienced qualitative researcher. Sampling sufficiency will be monitored on an ongoing basis throughout the data collection period, and this process will similarly consider the richness and diversity of the data obtained from the participant sub-groups involved. Recordings will be transcribed verbatim by a professional transcription company. Data will be analysed thematically and managed with the support of NVivo qualitative data software (Lumivero, Version 13, released March 2020). Regular meetings involving three members of the research team will aim to achieve consensus during coding, resulting in final, agreed themes for subsequent dissemination. The research team will follow guidance published in ‘Standards for reporting qualitative research: a synthesis of recommendations’ (SRQR).

### Safety reporting

All interventions in ENHANCE-D are licensed products with well-established safety profiles. The side effects for NRT products are extensively documented; therefore, several adverse events of interest relating to ECs will be collected at the follow-up timepoints (see schedule of events). The pre-specified AEs are shortness of breath, cough, phlegm, nausea, throat/mouth irritation, sleep disturbance, headache, mouth dryness, and dizziness. There is also an option for investigators to record other unspecified adverse events. Serious adverse reactions (defined as any untoward medical occurrence that results in death, is life-threatening, requires inpatient hospitalisation or prolongation of existing hospitalisation, results in a significant disability/incapacity or consists of a congenital anomaly or birth defect) which are judged to be related to the use of NRT/EC, will also be reported (prior to protocol version 5 [16SEP2024] any event meeting the criteria of an SAE was reported).

## Trial oversight committees and monitoring

The Trial Management Group (TMG) will be responsible for the day-to-day running of the trial and will comprise the CI, co-investigators, members of NCTU, statistician(s), sponsor, and, as required, other members of the co-applicant team. The TMG will monitor all aspects of trial conduct and progress, protocol adherence and take appropriate action to safeguard participants and the quality of the trial itself. The TMG will centrally monitor recruitment, data collection rates and protocol compliance. The TMG will meet every 4–6 weeks. The Trials Unit will perform onsite monitoring once during the trial in at least 50% of sites to ensure GCP compliance and protocol adherence. An Independent Data Monitoring Committee (IDMC) and Trial Steering Committee (TSC) will be established as per NIHR guidance [53], composed of independent experts in the field (clinicians and statisticians) and patient and public representatives (see Additional file 1 for full composition). The role of each committee is defined in their Charter. No formal interim analysis is planned. The IDMC will make recommendations to the TSC as to whether there are any ethical or safety issues that may necessitate changes to the trial.

